### Primary outcome measures

The primary outcome measures of safety are the number of patients with GBS treated with SVPE developing severe sepsis or septic shock (Additional file 1 for standardized definitions: Appendix 1A) due to CLABSI [22] and the occurrence of venous thrombosis in the limb where the CVC is placed (Additional file 1 for standardized definitions: Appendix 1B). The primary outcome measure of feasibility is the ability to remove at least 8 L of plasma over 8 days.

### Secondary outcome measures

The secondary outcome measures of safety of SVPE are the relative risk of CLABSI due to SVPE compared to CLABSI in control patients without GBS treated using a CVC, hemodynamic instability during the SVPE procedure (variations in systolic blood pressure greater than 30 mmHg or sudden bradycardia involving a reduction in heart rate by more than 20 beats per min within 30 min of starting SVPE or an increase in heart rate above 120 beats per min), and development of anemia (Hb < 8 g/dL) or serious hemorrhage requiring blood transfusion.

The secondary outcome measures of the feasibility of SVPE are the rate of CVC occlusion during the SVPE procedure, the healthcare personnel’s acceptability and satisfaction with the SVPE procedure, and any unanticipated events compromising the SVPE procedure as assessed using a standard questionnaire (Additional file 1 for standardized definitions: Appendix 1C). In addition, neurological outcome will be assessed in terms of improvement in GBS disability score [23] and MRC sum score [24] at discharge and up to 4 weeks after entry.

### Attempts to minimize the risks associated with SVPE

All connection ports of the SVPE kit (Fig. 2), the lumens of the CVC, the blood bag, and the saline bag will be disinfected with 70% alcohol and then air-dried before sampling blood or disconnection. Strict aseptic procedures will be followed to prevent CLABSI [25–27]. The SVPE procedure will not be started or stopped temporarily after the start of SVPE in patients who develop hypotension (30 mmHg decrease in systolic blood pressure, systolic blood pressure < 90, or MAP < 65 mmHg) or cardiac arrhythmia for any reason. After correction of hypotension and/or cardiac arrhythmia, the SVPE procedure will be started or restarted if SVPE stopped due to autonomic instability. The CVC will be removed as soon as SVPE is completed or the CVC will be immediately relocated to another insertion site if a CLABSI related to the CVC used for SVPE is confirmed or strongly suspected. Patients with GBS having severe sepsis as per standardized definition (Additional file 1: Appendix 1A) due to any organ site-specific infection present on admission (except for aspiration pneumonia) will be excluded for SVPE. Otherwise, any covert infection or aspiration pneumonia, as may be indicated by leukocytosis, will be investigated and treated accordingly after consultation with a medical microbiologist. Normal hemoglobin concentration for > 18 years man and non-pregnant woman will be considered as 13 and 12 g/dL, respectively [28]. However, blood transfusion will be considered to correct severe anemia (hemoglobin level < 8 g/dL [28]) before, during, or after SVPE. Proper screening of FFP for specific infective agents (hepatitis B and C viruses, human immunodeficiency virus (HIV), and syphilis) will be performed prior to administration of FFP.

**Fig. 2 Fig2:**
[figure not shown]
Illustration of the small volume plasma exchange (SVPE) kit. A SVPE kit will be prepared with one blood transfusion set and two saline infusion sets connected via a tri-channel device. The blood transfusion set will be connected to the blood bag and a saline infusion set will be connected to 1 L normal saline mixed with 2500 units of unfractionated heparin and the other ends of the blood transfusion and saline infusion sets will be connected with one lumen of the central venous catheter using a tri-channel device. Another saline infusion set will be connected to 500 mL hexa-ethyl starch solution and the other end connected with the second lumen of the central venous catheter. Air should be eliminated from all tubes using fluid from the respective bags

### Documentation (Table 1)

#### Baseline assessment and re-evaluation

Complete blood counts, including hemoglobin (g/L), erythrocyte sedimentation rate (ESR), C-reactive protein, and coagulation profile as well as serum calcium, magnesium, albumin, creatinine, bilirubin, and SGPT will be documented as baseline assessments for patients with GBS treated with SVPE, along with screening for hepatitis B, C, and HIV. Baseline assessments will be re-evaluated on day 4 (interim analysis) and day 10 (second day after completion of SVPE and removal of the CVC) after initiation of SVPE.

**Table 1 Tab1:** Standard Protocol Items: Recommendations for Interventional Trials (SPIRIT) table for the SVPE safety and feasibility study

	Study period							
	Enrolment	Allocation	Post-allocation					Close-out
	Entry^a^	0	Day 1–3	Day 4	Day 5–8	Day 10	Discharge*	Day 30*
Time point								
Eligibility screen	+							
Informed consent	+							
Allocation		+						
Interventions								
SVPE			+	+	+			
Non-SVPE			+	+	+			
Assessments								
SVPE procedure^b^			+	+	+			
Hemodynamic^c^	+	+	+	+	+	+	+	
Biochemistry^d^	+	±‡	±‡	+	±‡	+		
Infection screening^e^	+	±‡	±‡	+	±‡	+		+
Neurological^f^	+	+		+		+	+	+

*For patients treated with SVPE. ‡ Assessed as per indication

^a^Within 14 days of onset of muscle weakness

^b^Number and duration of each SVPE session and volume of the plasma removed and the replacement fluid infused

^c^Blood pressure, heart rate, body temperature, and pulse oximetry

^d^Hemoglobin (g/L), coagulation profile, serum level of calcium, magnesium, albumin, renal, and liver function test

^e^Complete blood count, erythrocyte sedimentation rate (ESR), C-reactive protein, and microbiological investigations to assess CLABSI, CAUTI, and VAP

^f^GBS disability score and MRC sum score

#### The procedure, hemodynamic parameters, and cost for SVPE

SVPE will be documented in terms of the duration and amount of plasma removed in each session, the type and volume of replacement fluid, and FFP used (Fig. 3). Throughout the procedure, hemodynamic status including blood pressure, heart rate, any cardiac arrhythmia, oxygen (%) saturation in peripheral blood, and fluid intake and output will be monitored daily according to the protocol. Autonomic parameters especially the presence of high or low blood pressure, increased or decreased pulse rate, and cardiac arrhythmia will be monitored and treated accordingly, before and after each SVPE session (12 times a day) and if necessary during and in between the SVPE sessions. Bladder and gastrointestinal dysfunction, pupillary abnormality, unusual sweating, and hyper-salivation will also be monitored daily. Any inconvenience experienced by the patient, nurse, or physician that temporarily or permanently compromise the SVPE sessions (Additional file 1 for standardized definitions: Appendix 1C). The cost for the SVPE in total 8 days will be approximately 500 US$ [fresh frozen plasma (24 bags) = 240 US$, blood bag and saline sets: 40 US$, low molecular weight heparin: 110 US$, routine investigation: 50 US$, saline: 10 US$, CV catheter: 40 US$ = total 490 US$].

**Fig. 3 Fig3:**
[figure not shown]
SVPE procedure for patients with GBS. A loading dose of low-molecular weight heparin (1.5 mg/kg) will be given subcutaneously at least 2 hours before initiation of SVPE; the same dose will be administered once daily or divided into two equal doses daily for 8 days or until SVPE is completed. Whole blood (7 mL/kg body weight) will be drawn from the central venous catheter into the blood transfusion bag in each session. The blood bag will be hung beside the patient for 2.5 h on a saline stand and left uninterrupted to allow plasma and blood cells to separate. The blood cells will be infused back into the patient and plasma will be discarded and replaced with fresh frozen plasma and colloid solution alternately (in equal volumes) via the closed-circuit SVPE kit illustrated in Fig. 2. In case of excessive clotting (bleeding time reduction of > 50% of baseline for that patient), aspirin (600 mg) will be administered orally at least 2 hours before the next SVPE session and continued thereafter at 150 mg orally/day until SVPE is completed. One blood bag will be used each day, with a total of six sessions/day. A total of 48 sessions will be performed over 8 days, removing approximately 8000 mL plasma in total

#### The hospital-acquired infections (HAI) and complications

CLABSI and primary and secondary bloodstream infections [22], catheter-associated urinary tract infection (CAUTI) [29], ventilator-associated pneumonia (VAP) [30], and other HAIs [31, 32] will be stringently documented in SVPE treated patients with GBS and non-GBS baseline control patients requiring the CVC in the ICU/HDU area using predefined criteria. Sepsis and severe sepsis will be documented as per protocol definition (Additional file 1 for standardized definitions: Appendix 1A). All cases of definite or strongly suspected CLABSI related to SVPE will be followed up until discharge to document the severity of CLABSI. Appropriate clinical data, imaging, and biochemical and microscopic analyses of specimens and bacteriological cultures will be documented as per indication of site-specific infections. Device-associated complications including CVC occlusion, hemorrhage, and deep vein thrombosis [33] will be documented in real-time.

#### Neurological function

Neurological examinations will be performed to monitor the clinical changes in motor, sensory, and autonomic parameters before and during the procedure and in the subsequent follow-up of patients lasting up to 4 weeks. Disability and motor function will be assessed using the GBS disability score [23] and MRC sum score [24]. Somatic and proprioceptive sensation of the limbs will be assessed bilaterally.

### Sample size

This safety and feasibility study will enroll 20 patients with GBS for SVPE. We cannot perform a formal power calculation for this safety and feasibility study. The sample size is based on previous pilot studies in GBS [34, 35]. The baseline rate of CLABSI will be measured in parallel in patients without GBS (and not undergoing SVPE) admitted to the same study facility who require a CVC during the study period. All control patients available during the inclusion time period will be included. We expect to obtain at least 20 or more (i.e., the maximum number of patients possible during the study period) control patients without GBS who require a CVC for at least 2 days and maximum of 8 days.

### Indication to stop the trial

Decision to stop the SVPE trial will be designated as per a Bayesian approach [36–38]. Accordingly, a predictive success rate of 75% will be set for the SVPE procedure. If more than 5 of 20 patients experience an SAE or when it appears to be impossible to remove at least 8 L of plasma in at least 15 individual patients, the procedure will be considered unsafe or unfeasible, respectively.

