**Methods:**

A total of 20 adult patients with GBS will be enrolled for SVPE at a single center in Bangladesh. Six daily sessions of whole blood sedimentation and plasma removal will be performed in all patients with GBS with a target to remove an overall volume of at least 8 liters (L) of plasma over a total of 8 days. Serious adverse events (SAE) are defined as the number of patients developing severe sepsis associated with the central venous catheter or deep venous thrombosis in the limb where the catheter is placed for SVPE. Based upon a predictive success rate of 75%, the SVPE procedure will be considered safe if less than 5 of 20 SVPE-treated GBS patients have a SAE. The procedure will be considered feasible if 8 L of plasma can be removed in at least 15 of 20 patients with GBS who receive SVPE. In addition, detailed clinical and neurological outcome assessments will be performed until discharge of the patient from the hospital and up to 4 weeks after study entry.

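### The stopping decision is labelled Bayesian with a 75% predictive success rate, but the rule printed is a raw count of 75% of 20: its safety part cannot trigger before the sixth SAE, and passing at 15 of 20 does not demonstrate 75%

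*Protocol article*

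**What the plan says.** The section Indication to stop the trial opens: "Decision to stop the SVPE trial will be designated as per a Bayesian approach". It continues that "a predictive success rate of 75% will be set for the SVPE procedure", and presents the decision rule as what follows from this. The rule has two parts:

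- Safety: "If more than 5 of 20 patients experience an SAE", the procedure is considered unsafe.
- Feasibility: "when it appears to be impossible to remove at least 8 L of plasma in at least 15 individual patients", it is considered unfeasible.

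The Abstract (Methods) also starts from the 75% ("Based upon a predictive success rate of 75"%), but there "the SVPE procedure will be considered safe if less than 5 of 20 SVPE-treated GBS patients have a SAE". Sample size fixes the denominator: "This safety and feasibility study will enroll 20 patients with GBS for SVPE". It also says that no formal power calculation could be done.

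Data management gives an independent DSMB responsibility for safety review, with adverse events reported to it within 24 hours, but no numeric limit. The only use of the term interim analysis (Baseline assessment and re-evaluation) is each patient's day-4 reassessment, which is not a look at the trial as a whole.

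**The concern.** A Bayesian monitoring rule updates a probability as patients accrue and acts when that probability crosses a stated value. The printed rule does neither. It fixes one count for 20 patients, whatever the number treated so far.

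Two consequences follow. First, as a stopping rule the safety part is inert early on. The SAEs here are severe sepsis from the catheter and thrombosis in the catheterised limb, and the Discussion calls catheter infection the major safety concern, so early events are the ones a stopping rule should respond to. Second, as a success criterion, a result that just passes says much less than a 75% predictive success rate suggests. A reader deciding whether to support the planned efficacy trial could take it as evidence that 75% has been reached.

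**Working it through.** **Inputs.** n = 20 (Sample size); target 75% success, so 25% failure (Indication to stop the trial); unsafe at more than 5 SAEs (same section); safe at fewer than 5 (Abstract); feasible at 15 or more. The document gives no prior or probability cut-off. Those used below are assumptions, and a range is shown.

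**1. The plan's own figure.** 0.75 × 20 = 15 successes, so 20 − 15 = 5 failures allowed. The stopping counts reproduce as a plain proportion. The Abstract's fewer than 5 SAEs means at least 16 of 20, or 80%. Exactly 5 SAEs is therefore neither safe (Abstract) nor unsafe (stopping section).

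**2. Early behaviour of the safety part.** With a Beta(a, b) prior on SAE risk and k SAEs in n patients, the posterior is Beta(a + k, b + n − k). Under the uniform prior, 3 of 3 gives 1 − 0.25⁴ = 0.996 and 5 of 5 gives 1 − 0.25⁶ = 0.9998.

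| SAEs so far | P(risk > 25%), Beta(1,1) | P(risk > 25%), Beta(0.5,1.5) | Predictive P(finishing with ≤ 5), Beta(1,1) | Printed rule triggers? |
|---|---|---|---|---|
| 3 of 3 | 0.996 | 0.984 | 0.003 | No |
| 4 of 5 | 0.995 | 0.986 | 0.002 | No |
| 5 of 5 | 0.9998 | 0.999 | < 0.001 | No |

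Beta(0.25,0.75) gives 0.993, 0.991 and above 0.999 for the same rows.

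**3. What a pass shows.** At 15 of 20 the exact (Clopper-Pearson) 95% interval is 0.509 to 0.913. P(success ≥ 75%) is 0.433 (uniform), 0.482 (Jeffreys), and 0.53 with either Beta(0.5,1.5) or Beta(0.25,0.75) on SAE risk. At 16 of 20 the interval is 0.563 to 0.943 and the uniform-prior probability is 0.633. By the binomial distribution, the chance of 5 or fewer SAEs is 0.617 at a true risk of 25%, 0.416 at 30% and 0.126 at 40%.

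**4. An illustrative boundary.** Trigger when P(SAE risk > 25%) ≥ 0.90 with Beta(0.5,1.5) (mean 0.5/2 = 25%), checked after each patient from the third, keeping the existing count of 6 as a separate ceiling. This gives 3 SAEs in the first 3–5 patients, 4 in 6–8, 5 in 9–11, then 6. Exact recursion over 20 patients, treating a trigger as a stop:

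| True SAE risk | Stop probability, count vs boundary | Mean patients | Mean SAEs |
|---|---|---|---|
| 10% | 1.1% vs 2.0% | – | – |
| 15% | 6.7% vs 8.8% | – | – |
| 25% | – | 18.5 vs 16.9 | 4.6 vs 4.2 |
| 30% | 58% vs 61% | 17.3 vs 15.1 | 5.2 vs 4.5 |
| 50% | – | 11.9 vs 8.0 | 6.0 vs 4.0 |

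SAEs saved: 4.6 − 4.2 = 0.4 at 25%, 5.2 − 4.5 = 0.7 at 30%, and 6.0 − 4.0 = 2.0 at 50%.

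**The case against.** The strongest reply has five parts.

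- **A count can encode a posterior rule.** Under Beta(0.5,1.5), P(SAE risk > 25%) is 0.467 at 5 of 20 and 0.660 at 6 of 20, so more than 5 of 20 is where the posterior first passes one half. This is true, but only at the final look. It says nothing about patients 3 to 19, and the section is about stopping.
- **The article condenses a fuller protocol and cites sources for its approach.** A missing prior alone would be no finding, and a reader should not infer that no Bayesian work exists. What stands is that the article presents the count as the consequence of the Bayesian approach, and the printed count does not behave as one during accrual.
- **The DSMB can act earlier.** A reader might infer that the trial would have run on regardless of early harm. The document does not support that: the DSMB is independent, includes a biostatistician and a microbiologist, and hears of adverse events within 24 hours. The feasibility wording may also allow an early stop, so the sixth-event limit applies to the safety part only. But the DSMB is given no other number to work with.
- **A pass at 15 of 20 need not mean odds below one half.** A reader might infer that it does. This depends on the prior, and two of the four priors tried give 53%. About even odds is as far as it goes.
- **The gain is modest near the threshold.** It is under one SAE at 25% to 30% risk, and five SAEs in five patients has probability 0.25⁵ = 0.1% at 25% risk and 0.5⁵ = 3% at 50%. The ceiling of 6 in the illustration is itself a count: the posterior there is 0.66 at 6 of 20, not 0.90. Both points are accepted.

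**Conclusion.** The concern holds in limited form. The label and the printed rule disagree. The safety part cannot trigger before the sixth SAE, although at 3 of 3, 4 of 5 or 5 of 5 the probability that risk exceeds 25% is about 98% or higher under the priors tried. A pass at 15 of 20 is compatible with a true success rate from 51% to 91% and carries about even odds of 75% or better, so it does not demonstrate 75%.

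The practical gain from a sequential boundary is small near 25% to 30% risk and clear only when the risk is high. These sizes rest on the assumed priors, the 0.90 cut-off and independent patients with a constant SAE risk. The interval, the binomial probabilities and the sixth-event property do not depend on a prior. Recruitment Status reports that all 20 patients had been treated by June 2017, so a boundary can no longer protect them. The labelling and reporting problem remains.

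**What to change.** **For this trial.** Describe the 15-of-20 and SAE criteria as count rules, without the Bayesian or predictive label. Report each verdict with its exact interval, or with a posterior probability whose prior is stated. Reconcile the Abstract's limit of fewer than 5 with the stopping section's more than 5, so that exactly 5 SAEs has one defined meaning. If a prior, cut-off or look schedule exists in the full protocol, state it. The cost is a few sentences and no new data. The reconciliation should be disclosed as made after recruitment ended.

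**For the planned efficacy trial, or any design reusing this rule.** Add a sequential safety boundary for DSMB review based on a stated posterior probability, with the prior and cut-off chosen by the DSMB. The boundary worked out above is an illustration of form, not a recommended limit. It needs one table row in the DSMB wording. Its statistical cost is the rise in false stops, from 1.1% to 2.0% at a true risk of 10% and from 6.7% to 8.8% at 15%. Define also what evidence makes the feasibility target appear out of reach.

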### Data management

The unique patient identity (ID), name, date of birth, and basic demographic and clinical data of the SVPE-treated patients and control patients will be stored separately in paper and electronic database documentation and updated on a daily basis. All the privacy-sensitive data will be stored encrypted. In case of withdrawal, follow-up and data collection will continue with the participant’s permission. A data safety monitoring board (DSMB) consisting of clinical experts, a microbiologist, and a biostatistician from the icddr,b ERC committee will be responsible for the monitoring and review of the safety and conduct of this safety and feasibility study. The DSMB will function independently and has the right to audit the study without notice to the investigators and the sponsor. Important protocol amendments for approval and AEs that occur at a greater frequency or intensity than expected will be reported to the IRB of the icddr,b within 7 business days. However, any AE without any discretion will be reported to the DSMB and the ERC within 24 h. Upon completion of the trial, all study-related data and trial documents will be archived securely at the icddr,b and retained for a minimum of 10 years. The corresponding author will have full access to all the data in the study and will be responsible for the decision to submit the publication.

### Statistical analysis

The rate of HAIs (CLABSI, CAUTI, VAP) per 1000 device days will be calculated by dividing the number of HAIs (CLABSI, CAUTI, VAP) during the study period by the number of device days and multiplying the result by 1000. The infection safety profile for SVPE will be assessed by calculating the standardized infection ratio (SIR) to define the risk of HAI in patients with GBS treated with SVPE. The SIR will be calculated by dividing the number of observed infections by the number of infections predicted (i.e., the infection rate in the control group). The predicted HAI rate will be calculated using the rates of HAI in the control group of patients without GBS during the study period. Percentage values will be compared using chi-square test or Fisher’s exact test (two-tailed) and median values, the Mann-Whitney *U* test using SPSS 22 software (IBM Corp. Released 2013. IBM SPSS Statistics for Windows, Version 22.0. Armonk, NY: IBM Corp). Analyses will be performed on an intention-to-treat basis. All *p* values reported will be two sided, and a difference of *p* < 0.05 will be considered significant*.*

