#### Patients without GBS

Patients ≥ 18-years of age with a diagnosis other than GBS requiring a CVC for > 2 to ≤ 8 calendar days after admission to the same ICU and HDU units in the same period of time will be eligible. Patients with healthcare-associated infection present on admission (except aspiration pneumonia) and pregnant women will be excluded from the control group.

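### Controls are selected on catheter duration at both ends while all device days are counted, so the CLABSI ratio of SVPE to control need not equal 1 under equal daily risk, and the direction of the bias is not fixed

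*Protocol article*

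**What the plan says.** **Rate and ratio.** In the protocol article, Statistical analysis, the rate per 1000 device days comes from "dividing the number of HAIs (CLABSI, CAUTI, VAP) during the study period by the number of device days". No device days are set aside. On the reference rate the section says: "The predicted HAI rate will be calculated using the rates of HAI in the control group of patients without GBS during the study period". On the ratio it says: "The SIR will be calculated by dividing the number of observed infections by the number of infections predicted (i.e., the infection rate in the control" (cut just before the bracket closes). Secondary outcome measures names the relative risk of CLABSI against controls as a safety outcome.

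**Controls.** The section Patients without GBS admits adults "requiring a CVC for > 2 to ≤ 8 calendar days after admission to the same ICU and HDU units". The Sample size section describes controls as patients "who require a CVC for at least 2 days and maximum of 8 days". The upper bound agrees, but the lower bound does not: more than 2 days in one place, at least 2 in the other.

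**SVPE patients.** The entry criteria under Patients with GBS contain no catheter-duration condition. The exposure is set by the procedure (Fig. 3): "A total of 48 sessions will be performed over 8 days, removing approximately 8000 mL plasma in total". On the end of catheter time, the section on minimizing risks says: "The CVC will be removed as soon as SVPE is completed or the CVC will be immediately relocated to another insertion site", the relocation applying to a confirmed or strongly suspected CLABSI.

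**Infection criteria.** Infections "will be stringently documented in SVPE treated patients with GBS and non-GBS baseline control patients requiring the CVC in the ICU/HDU area using predefined criteria". The CLABSI definition itself is in a cited source that is not shown.

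**The concern.** One group is selected on how long the catheter stayed in and the other is not, yet both rates are divided by all device days. If duration means realised duration, whether a patient becomes a control depends on what happens after insertion. Two distortions follow.

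- **Lower bound.** A line that comes out within the first two days, for infection or any other reason, never enters the control group. The first two days of every control are then guaranteed time, which adds to the denominator and contributes few or no events.
- **Upper bound.** A line that stays in beyond day 8 without infection is dropped, while a line ended by infection between day 2 and day 8 is kept. This removes infection-free time and raises the control rate.

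The Discussion calls catheter infection the major safety concern and says that no CLABSI data exist for Bangladeshi ICUs or HDUs. The concurrent controls are therefore the only local reference, and the SIR could mislead in either direction about the infection risk of SVPE.

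**Working it through.** The plan states no SIR or predicted rate, so there is no figure to reproduce. The check asks what the SIR would be if the true daily risk were the same in both groups. It should be 1.

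**Inputs from the protocol:** control duration above 2 and up to 8 days; SVPE about 8 catheter days; denominator of all device days; 20 SVPE patients and 24 controls (Recruitment status); 6.8 CLABSI per 1000 central line-days (Discussion), used only for scale.

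**Assumptions, not in the documents:** constant daily infection risk h = 0.0068; constant non-infectious removal at rate 1/m, with m from 2 to 15 days; infection ends the catheter in controls; eligibility follows realised duration T. Write λ = h + 1/m.

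**Case 1, SVPE at risk from day 1.** The SVPE rate is h.

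- *Controls with 2 < T ≤ 8, longer catheters excluded.* Control rate = (h/λ) / E[T | 2 < T ≤ 8], so null SIR = λ × E[T | 2 < T ≤ 8], where E[T | 2 < T ≤ 8] = 2 + 1/λ − 6e^(−6λ)/(1 − e^(−6λ)). For m = 2: λ = 0.5068, the conditional mean is 2 + 1.672 = 3.672, and SIR = 0.5068 × 3.672 = 1.86. For m = 15: λ = 0.0735, the mean is 4.780, and SIR = 0.35.
- *Controls with T > 2, censored at day 8.* Null SIR = λ × [2 + (1 − e^(−6λ))/λ] / (1 − e^(−6λ)) = 1 + 2λ/(1 − e^(−6λ)).

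**Case 2, first two days event-free in both groups** (as if the CLABSI definition did not count them; an assumption). The SVPE rate becomes h × 6/8, so the SIR with longer catheters excluded is 0.75 times the Case 1 value.

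| Mean removal time m (days) | Case 1, beyond day 8 excluded | Case 1, censored at day 8 | Case 2, beyond day 8 excluded |
|---|---|---|---|
| 2 | 1.86 | 2.06 | 1.40 |
| 3 | 1.38 | 1.78 | 1.03 |
| 4 | 1.09 | 1.65 | 0.82 |
| 5 | 0.91 | 1.58 | 0.68 |
| 7 | 0.68 | 1.51 | 0.51 |
| 10 | 0.50 | 1.45 | 0.38 |
| 15 | 0.35 | 1.41 | 0.26 |

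The ratio crosses 1 between m = 4 and 5 in Case 1 with exclusion, and between m = 3 and 4 in Case 2. With censoring, Case 1 stays above 1 throughout.

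**Candidate remedies.** Suppose only days and infections after day 2 count, in both groups. If longer catheters are still excluded, the null SIR is λ × E[T − 2 | 2 < T ≤ 8], which is 0.5068 × 1.672 = 0.85 at m = 2 and falls to 0.20 at m = 15. If longer catheters are kept and censored at day 8, control events are (h/λ)(1 − e^(−6λ)) and control time is (1 − e^(−6λ))/λ. The control rate is then h and the null SIR is 1.00 at every m.

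**Scale.** Expected control CLABSIs are 24 × 3 × 0.0068 = 0.49 to 24 × 8 × 0.0068 = 1.31. The chance of no control event, and so an undefined SIR, is e^(−0.49) = 0.61 to e^(−1.31) = 0.27. SVPE patients expect 20 × 8 × 0.0068 = 1.09 events.

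**The case against.** A reader might infer something stronger: that the first two control days are event-poor, so the control rate is understated and the SIR is pushed above 1. Taking 2 event-free days in controls only, that reading gives d/(d − 2), or 2.00, 1.67 and 1.50 for control stays of 4, 5 and 6 days. The documents do not support it, for three reasons.

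- That the days are event-poor is an inference. The CLABSI definition is not shown. If it does discount early events, the same criteria are applied to SVPE patients. With 8 SVPE days the ratio is then 0.75d/(d − 2): 1.50, 1.25 and 1.13 for the same stays, and 1.00 at 8 days.
- The wording speaks of patients who require a catheter. That can be read as need, so that replacing an infected line on day 1 or 2 would not end eligibility.
- The same sentence has an upper bound, and under exclusion it works in the opposite direction.

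The remaining objections are about importance. The comparison is secondary, and the primary safety judgement counts serious events among SVPE patients only. With about one expected event per group, sampling error will usually exceed this bias. Infections per 1000 device days is also a conventional rate. All of this stands and limits the weight of the point. It does not remove it: the article itself states both the selection rule and the formula, and together they need not give 1 under equal risk.

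**Conclusion.** The point holds as a comparability defect of unknown direction in a secondary safety measure. If eligibility follows realised duration, the null SIR lies between 1.86 and 0.35 when catheters lasting beyond day 8 are excluded, and between 2.06 and 1.41 when they are censored, for SVPE patients at risk from day 1. These figures rest on constant hazards, infection ending the control catheter, a rate of 6.8 per 1000 and the assumed removal times; no control dwell times are given. Neither a net upward bias nor a fixed percentage understatement of the control rate can be claimed. If eligibility follows the need for a catheter, whatever happens to a particular line, the selection argument weakens, so the protocol should say which is meant. Correcting only the lower end would not be safe: if longer catheters remain excluded, it leaves a ratio of 0.85 to 0.20, which would make SVPE look too safe.

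**What to change.** - For the SVPE-versus-control CLABSI ratio, use one at-risk window in both groups: catheter days 3 to 8, and infections arising in those days.
- Keep controls whose catheter stays in longer than 8 days and censor them at day 8.
- Define expected CLABSIs as control infections per at-risk day multiplied by SVPE at-risk days. This also settles the current wording, which equates a predicted number with a rate.
- Report SVPE infections on days 1 and 2 separately, so that no early safety event is lost from view.
- Keep the rate per 1000 device days as a descriptive figure.
- Reconcile the minimum control duration between Patients without GBS and Sample size, and state whether the 8-day limit excludes or censors.

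The cost is analysis wording and a small change to the control rule. Recruitment is reported as complete, so if patients with longer catheters were left out, their dates and infections would have to be recovered from unit records, or the residual bias stated as a limitation. The statistical price is fewer catheter days in an already sparse comparison. The primary safety rule is unaffected.
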